# Evaluating Mobile Apps and Biosensing Devices to Monitor Physical Activity and Respiratory Function in Smokers With and Without Respiratory Symptoms or Chronic Obstructive Pulmonary Disease: Protocol for a Proof-of-Concept, Open-Label, Feasibility Study

**DOI:** 10.2196/16461

**Published:** 2020-03-26

**Keywords:** COPD, mobile health apps, mHealth, smokers, feasibility study

## Abstract

**Background:**

Chronic obstructive pulmonary disease (COPD) is a global public health problem, and continuous monitoring is essential for both its management as well as the management of other chronic diseases. Telemonitoring using mobile health (mHealth) devices has the potential to promote self-management, improve control, increase quality of life, and prevent hospital admissions.

**Objective:**

This study aims to demonstrate whether a large-scale study assessing the use of mHealth devices to improve the treatment, assessment, compliance, and outcomes of chronic diseases, particularly COPD and cardio-metabolic syndrome, is feasible. This will allow our team to select the appropriate design and characteristics for our large-scale study.

**Methods:**

A total of 3 cohorts, with 9 participants in each, will use mHealth devices for 90 days while undergoing the current standard of care. These groups are: 9 “non-COPD,” otherwise healthy, smokers; 9 “grey zone” smokers (forced expiratory volume in 1 second/ forced vital capacity ≥0.70 after bronchodilator treatment; COPD Assessment Test ≥10); and 9 smokers diagnosed with Stage 1-3 COPD. Rates of recruitment, retention, and adherence will be measured. Overall, two mHealth devices will be utilized in the study: the AnaMed Original Equipment Manufacturer device (measures distance, energy expenditure, heart rate, and heart rate variability) and the Air Next mobile spirometry device. The mHealth devices will be compared against industry standards. Additionally, a questionnaire will be administered to assess the participants’ perceptions of the mHealth technologies used.

**Results:**

The inclusion of participants started in June 2019. Study results will be published in peer-reviewed scientific journals.

**Conclusions:**

This study will demonstrate whether a large-scale study to assess the use of mHealth devices to improve the treatment, assessment, compliance, and outcomes of chronic diseases, particularly COPD and cardio-metabolic syndrome, is feasible. It will also allow the research team to select the appropriate design and characteristics for the large-scale study.

**Trial Registration:**

ClinicalTrials.gov NCT04081961; https://clinicaltrials.gov/ct2/show/NCT04081961

**International Registered Report Identifier (IRRID):**

DERR1-10.2196/16461

## Introduction

Chronic obstructive pulmonary disease (COPD) accounted for 3.2 million deaths globally in 2015 [1] and is the fourth leading cause of death both worldwide and in Kazakhstan [2]. COPD is a heterogeneous condition, with a variety of disease-related phenotypes [3,4], and its main risk factor is cigarette smoking [5]. The chronic airflow limitation that characterizes COPD is caused by obstructive bronchiolitis and parenchymal destruction (emphysema). Pulmonary emphysema is a form of COPD; however, pulmonary emphysema without airway obstruction is common in smokers [6,7]. Smokers with symptoms suggestive of COPD who do not qualify for a diagnosis of COPD based on spirometry are referred to as “grey zone” COPD patients. They have preserved pulmonary function (forced expired volume in 1 second/forced vital capacity [FEV_1_/FVC] of at least 0.70 after bronchodilator and FVC ≥80% of the expected value) and respiratory symptoms (COPD assessment test [CAT] ≥10).

Continuous monitoring is vital for the management of COPD. Implementing telemedicine and mobile health (mHealth) innovations has allowed clinicians to intervene in COPD earlier and prevent complications. However, there remain challenges in the form of alarm frequency and response, both of which need to be implemented into the existing workflow [8]. Data flow and workflow processes need to be designed with precision at the outset if telemedicine is to be applied in clinical practice. Telemonitoring using mHealth devices has the potential to promote self-management, improve control, increase quality of life, and prevent hospital admissions [9-13]. Technological advances in mHealth home telemonitoring (electronic health [eHealth]) programs and systems can affect care for patients with COPD [12,14-17]. mHealth devices are an emerging opportunity in clinical studies, and their utility (ie, sensitivity, accuracy, and reproducibility) has previously been assessed for telemonitoring for COPD [14].

Telemonitoring is a promising alternative or adjunct to the provision of traditional health care services in COPD [18]. Although some studies have shown that telemonitoring may improve some clinical outcomes and reduce health care costs [19,20], the effects of telehealth interventions on emergency department attendance, hospital admissions, duration of admissions, health-related quality of life, costs, and mortality remain less certain [18,21-25].

In a recent study of telemedicine in the home setting using multiple activity sensor monitoring equipment in COPD patients, the augmentation of traditional telemedicine methods with motion sensing, spirometry, and symptom diaries appeared feasible [26]. In a literature review (141 randomized trials; n=37,695) of studies of eHealth practices, such as telemetry, telephone calls, or home visits by nurse specialists, most studies were relatively short term (<6 months) and did not yield strong evidence for telemedicine use in the management of chronic diseases [27]. However, the comparison of outcomes in studies using telehealth applications is difficult due to advances in monitoring and communications technology and heterogeneity in the type of monitoring, the disease entity and severity, and the variations in the process of care brought about by the telemedicine intervention [12].

Although peak flow monitoring has been used for at-home detection of asthma exacerbations, and studies in the past have monitored vital signs and symptoms in patients with COPD [28], few studies have attempted to deploy spirometry for home monitoring of COPD [29]. With technical advances, spirometry is increasingly being used to track the progress of COPD over time and to identify acute exacerbations [30-34].

While the number of COPD mHealth devices is rapidly increasing, most have not been validated as clinically effective tools for the management of the disease. In addition to empowering patients and facilitating disease self-management, mHealth offers promising aid to COPD researchers to help them personalize treatments based on patient-specific profiles and integrate symptom occurrence and medication usage with environmental and genomic data. An integrated and targeted practice-managed approach that uses mHealth technologies in primary care settings will be most effective for the early identification, monitoring, and management of chronic diseases, particularly COPD and cardio-metabolic syndrome (ie, combined diabetes mellitus, systemic arterial hypertension, central obesity, and hyperlipidemia). Health information technologies are revolutionizing health care by assisting patients in self-monitoring and decision-making, driving a shift toward a care model increasingly centered on personal use of digital and web-based tools [35-37]. Because there is a dearth of evidence that direct-to-consumer mHealth tools are effective or that they provide accurate disease recommendations, they are not yet widely used in clinical practice. Nonetheless, the preponderance of mHealth is gradually increasing in health care, industry, and as a subject of research [38].

This study aims to investigate the feasibility and utility of using mHealth devices to improve the treatment, assessment, compliance, and outcomes of smokers with and without respiratory symptoms/COPD. It namely means to assess the feasibility of mHealth devices in current smokers with and without respiratory symptoms or COPD by monitoring physical activity, vital signs, and respiratory function, and aims to assess the validity of mHealth devices in detecting vitality parameters as compared to industry standards.

After demonstrating proof of concept in this study, its purpose will be to incorporate mHealth devices into an ongoing 5-year longitudinal cohort observational study to monitor selected vitality parameters and other comorbidities [39]. Specifically, depending on the outcomes of the study, the AnaMed Original Equipment Manufacturer (OEM) device and the Air Next mobile spirometer will be introduced to record data from a randomized subsample of participants in an observational cohort study, including smokers of combustible cigarettes and users of IQOS with HeatSticks.

## Methods

### Study Design

This is a proof-of-concept, open-label, three-arm, observational, single-center feasibility study. A total of 27 participants in three cohorts will use the mHealth devices for 90 days while undergoing the current standard of care based on their smoking disease state or lack of disease state. The groups are made up of nine “non-COPD,” otherwise healthy, smokers, nine “grey zone” smokers (ie, FEV_1_/FVC ≥0.70 after bronchodilator treatment, CAT ≥10; six-minute walk test [6MWT]<450 meters), and nine smokers diagnosed with Stage 1-3 COPD.

In each group, nine participants will be randomly assigned to three types of reminders: three participants will be reminded every morning by text message or phone call and contacted every evening by phone or chat services (eg, Skype, WhatsApp, Viber, texting) to share their experiences and feedback on mHealth device usage; three participants will receive only morning reminders; and three participants will receive neither morning reminders nor evening communication/feedback.

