#### Participant Recruitment and Registration

We will employ various nonprobability sampling techniques, including quota and snowball sampling methods, to recruit study participants. The Kazakhstan Academy of Preventive Medicine research team will register patients for each mHealth device. Installation and user guides for each technology used include labeled photographs and written instructions to be used by all teams and patients during setup. All equipment has been tested before deployment. Training is provided on setup, installation, and use as well as individual checklists, decision trees, and troubleshooting information. The break for charging is at a standard time (20:00) across arms. In addition to direct phone communication, WhatsApp, texting, and other types of messaging systems are used for sharing daily experiences each evening to assist with assessing the level of comfort and address issues with wearing the AnaMed OEM device and using the Air Next mobile spirometer.

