### Statistical Analysis

For this proof-of-concept phase, access to device-derived data will be enabled via a cloud-to-cloud solution. Graphical and statistical comparisons will be made between the mobile biosensing device–derived data and the data derived from the clinical standards, and between the three different study groups. Descriptive statistics will be used to summarize required qualitative and quantitative study elements (eg, proportion, mean, standard error, median, interquartile range, 95% confidence interval).

The exploratory graphical analysis will be done before the numerical analysis. Histograms and two-dimensional scatterplots of raw data will provide information on the univariate and bivariate distributions of the variables, focusing on the distribution of variables and relationships between the variables (whether there is a linear or nonlinear relationship). Additionally, preliminary graphs will be used to screen raw data by highlighting obvious data errors. Tabulations will be produced for appropriate disposition, demographics, baseline, safety, and clinical parameters.

Statistical comparisons will be made between the mobile biosensing device–derived data and the data derived from the standard diagnostic equipment and methods. Agreement analysis will be performed for both binary and quantitative measures. For binary variables, percent of agreement (overall, positive, and negative agreement) as well as Kappa coefficient, *P* value, and 95% confidence interval will be calculated. For two quantitative measures of a parameter, we will use the Bland-Altman method (Bland-Altman plot and limits of agreement). The Bland-Altman plot analysis will allow us to evaluate a bias between the mean differences and to estimate an agreement interval, within which 95% of the differences between two quantitative methods of measurement are included. Correlation analysis will also be run so that Pearson’s correlation coefficient and the 95% confidence interval will be calculated.

The agreement analysis will be done for baseline, 7-day, 14-day, 21-day, 28-day, 56-day, and 90-day visits separately and for the data pooled from all measurements. Within-Subject study design will be accounted for to assess accuracy and precision for a single mobile device. All statistical analyses will be done for all participants and by study group. Additionally, we will compare trends of binary and quantitative outcomes from three study groups wearing mobile devices.

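### Reminder schedule is the only randomised factor and bears on adherence, a primary endpoint, yet the analysis does not use it, and the text leaves open who receives evening contact

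*Protocol article*

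**What the plan says.** **Assignment.** Under Study Design, "A total of 27 participants in three cohorts will use the mHealth devices for 90 days", and "In each group, nine participants will be randomly assigned to three types of reminders". The three types are:

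- A: "three participants will be reminded every morning by text message or phone call and contacted every evening by phone or chat services"
- B: "three participants will receive only morning reminders"
- C: "three participants will receive neither morning reminders nor evening communication/feedback"

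**Endpoint.** Outcome Measures makes recruitment, retention, adherence and safety the primary measures. Adherence is all-or-nothing for each person: a participant counts only if every device parameter was recorded on every day. It is a single proportion of those enrolled. Sample Size Calculation assumes 70% and gives a precision of 17%, again for one rate.

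**Analysis.** Statistical Analysis plans agreement between device and clinical standard, comparisons and trends across the three study groups, and then fixes the strata: "All statistical analyses will be done for all participants and by study group". Reminder type is not mentioned there, in Outcome Measures or in Sample Size Calculation.

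**Evening contact elsewhere.** Participant Recruitment and Registration says that phone, WhatsApp, texting and other messaging "are used for sharing daily experiences each evening to assist with assessing the level of comfort and address issues with wearing" the wearable and using the mobile spirometer. No subset of participants is named.

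**The concern.** Cohort is fixed by disease status. Reminder schedule is the only thing that the article allocates at random, and its evident target is daily device use, which is what the adherence endpoint counts. A plan that randomises this factor and then names only cohort as a stratum gives up its one unconfounded comparison. The pooled adherence rate mixes three levels of support in equal parts. The Objective section says that the study should help select the design and characteristics of the large-scale study, and the amount of contact that participants need is one such characteristic.

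The second strand concerns delivery. If staff took the recruitment section as a procedure for everyone, people assigned no evening contact would get it, and a later analysis by schedule could not recover the intended contrast.

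**Working it through.** **1. Allocation.** 3 per schedule in each cohort × 3 cohorts = 9 per schedule. B and C together make 9 + 9 = 18 of 27 who are assigned no evening contact.

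**2. Meaning of group.** Study Design randomises inside each group, so a group there is a cohort. On that usage, the group comparisons and strata in Statistical Analysis are by cohort, and no listed comparison is by reminder schedule.

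**3. The plan's own precision figures.** The formula is the two-sided Wald half-width, 1.96 × √(p(1 − p)/n), with n = 27.

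- Adherence, p = 0.70: 1.96 × √(0.21/27) = 0.173. Stated: 17%.
- Retention, p = 0.85 (15% dropout): 1.96 × √(0.1275/27) = 0.135. Stated: ±13%.

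Both agree with the stated figures to within rounding or truncation. The planned precision is therefore that of one rate over all 27.

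**4. Precision by schedule, on the protocol's adherence definition.**

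- One schedule, n = 9, p = 0.70: 1.96 × √(0.21/9) = 0.299, about ±30 points.
- Difference between two schedules, both at 0.70: 1.96 × √(0.21/9 + 0.21/9) = 0.423, about ±42 points.
- Exact 95% interval for 6 of 9 adherent: 30% to 93%.
- One schedule within one cohort, n = 3: 1.96 × √(0.21/3) = 0.519, about ±52 points. Even 3 of 3 against 0 of 3 gives Fisher P = 0.10.
- Power at 9 against 9 for an assumed 50% v 90%: 30% by Fisher's test, 45% by the normal approximation.

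For retention at 0.85 with n = 9, the same formulas give 1.96 × √(0.1275/9) = 0.233 per schedule and 1.96 × √(2 × 0.1275/9) = 0.330 for a difference. The Wald interval for one schedule then runs past 100% (0.85 + 0.233 = 1.083), so exact or score intervals are preferable at this size.

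**5. What pooling can hide (illustration with assumed rates).** Adherence of 85%, 70% and 55% in A, B and C averages (85 + 70 + 55)/3 = 70%. That equals the planning value while the schedules span 30 points. The half-width for the A–C difference would be 1.96 × √(0.85 × 0.15/9 + 0.55 × 0.45/9) = 0.400, about ±40 points. The study could show such a spread but could not distinguish it from zero.

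**6. Evening contact under the two readings.**

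| Schedule | As assigned in Study Design | If the recruitment text covers everyone |
|---|---|---|
| A | morning + evening | morning + evening |
| B | morning only | morning + evening (same as A) |
| C | neither | evening only |

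Under the second reading 18 participants receive contact that they were not assigned.

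**The case against.** **The recruitment section may simply describe how schedule A is delivered.** Its channels, its time of day and its purpose largely match the evening contact in Study Design, and nowhere does it say that all participants are contacted. This stands. A reader might infer that the two sections contradict each other and that the contrast will be erased, but the text does not go that far. What remains is that the sentence carries no restriction and directly follows one that fixes the charging break for all arms, so a general reading is also open.

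**A by-schedule breakdown may sit in the full protocol or analysis plan.** This is a fair caution for a condensed article, and the article does not forbid other breakdowns. It has less force than usual here, because the article does state its comparisons and strata and leaves out the randomised factor.

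**The numbers are too small to choose a regimen.** On the stated endpoint this is largely right, and it rules out a test. It does not rule out estimates: results are already planned by cohort, which is also 9 per group, and Limitations says that the study seeks parameter estimates for the main study.

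A reader might claim better precision by scoring each person's proportion of device-days. With an assumed between-person SD of 15 to 30 points, a difference would have a half-width of t(0.975, 16) × SD × √(2/9) = 2.12 × SD × 0.471, or about 15 to 30 points. The documents define no such endpoint and give no SD, so that range cannot be set against the protocol's adherence measure.

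**Conclusion.** The point holds in two parts of different strength.

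- **Firm, as the article is written:** reminder schedule is randomised with 9 per arm, bears directly on a primary endpoint, and appears in no outcome, precision or analysis statement.
- **Ambiguity only:** the article does not say whether the evening contact in the recruitment section is limited to the 9 participants assigned it. Applied to everyone, it would merge A with B and end C's no-contact condition.

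The gain from analysing by schedule is descriptive. At 70% adherence, expect about ±30 points per schedule and ±42 for a difference, assuming 9 analysed per schedule and Wald intervals.

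Two stronger conclusions are not supported. One is that the choice of main-study design is left without support: recruitment, retention, device agreement and user-experience data all inform it. The other is that the pooled rate describes no regimen that the main study would use: the documents do not say what reminders that study will have. The study remains usable. The change is worth making because it costs little and uses information already being collected.

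**What to change.** 1. **Participant Recruitment and Registration:** state which participants the evening sharing of experiences covers, so that it agrees with the assignment in Study Design. A record of the contacts actually made would let readers check that the schedules stayed distinct.
2. **Statistical Analysis:** add a descriptive summary of adherence, as defined in Outcome Measures, and of retention by randomised reminder schedule (9 each). Give pairwise differences and 95% confidence intervals, pooled over or stratified by cohort, beside the overall rate. Exact or score-based intervals suit these numbers.
3. **Same section:** say that this is estimation without a powered test, and quote the expected half-widths (about 30 points per schedule and 42 for a difference at 70% adherence).
4. **Optional:** report the proportion of device-days as a supplementary measure. It should not replace the primary definition, since the sample-size statement rests on that definition.

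The cost is a clarifying sentence, a short addition to the analysis text and one table. No extra participants or outcome data are needed. If contacts are not already recorded, a simple contact log would be the only new item.

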### Study Devices and Assessments

Two mHealth devices will be utilized in the study: the AnaMed OEM device (measures step counts, energy expenditure, heart rate, and heart rate variability) and the Air Next mobile spirometry device (Nuvoair AB, Stockholm, Sweden) (measures FEV_1_, FVC, and forced expiratory flow).

At the Kazakhstan Academy of Preventive Medicine COPD Center, standard spirometry data are collected by using the BTL-08 SPIRO (BTL Industries Limited, United Kingdom) spirometry system. The spirometer used in this study is tested and continuously standardized with a 3-liter syringe. Quality assessments will be performed throughout the study. The Vive Precision DMD 1003 pulse oximeter is used to get peripheral capillary oxygen saturation (SpO2) and pulse readings at the Kazakhstan Academy of Preventive Medicine COPD center and will be used for comparison to the results produced by the AnaMed OEM device.

### Outcome Measures

Safety and tolerability will be evaluated through adverse events (AEs), lung function tests, vital signs, and supportive care medications. Primary measures are defined as rates of recruitment, retention, and adherence as well as safety of the intervention that are common for feasibility studies [40]. Recruitment is defined as the number of potential participants screened for study eligibility versus the number of people who enrolled in the study. Retention is defined as the proportion of participants enrolled who completed the intervention and all study measures. Adherence to the study protocol is determined as the proportion of participants enrolled who had all their mHealth parameters registered every day.

The mHealth devices will be compared to the industry standards. Additionally, a questionnaire will be administered to assess the participants’ perceptions of the mHealth technologies used.

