### Sample Size Calculation

The primary endpoints of the study are rates of recruitment, adherence, and retention. To assess the feasibility of the intervention, we plan to recruit 27 participants, which should be enough to get estimates with a sufficient degree of uncertainty. We conservatively predict that 30% of the people invited to participate will be recruited to the study, with a 95% CI of 13-47%. We also assume the dropout rate will be 15%. The accuracy of the estimated retention rate will be at least ±13%. Further, we believe that 70% of participants will adhere to the use of mHealth devices. In this case, the accuracy of the estimate will be at least 17%. All calculations are based on two-way 95% confidence intervals.

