### Study Procedures

#### Overview

The study will last 90 days and has two stages. The first stage includes the initial period of using the mHealth devices (Days 1-21) to evaluate the validity of collecting vitality parameters (eg, heart rate, blood oxygenation, steps/motion) on mHealth devices. The main period of use for the mHealth devices (Days 22-90) is the second stage, which aims to evaluate the feasibility of participants using these devices. The schedule of enrollment and data collection is shown in Table 1.

For Table 1, spirometry was performed to diagnose and monitor COPD. Providing of mHealth devices involved the provision of the AnaMed OEM device, the Air Next mobile spirometer, and instructions/review of how to use these tools (print and verbal instructions). For the assessment of the AnaMed OEM device, the participants’ SpO2 will be measured at each visit using industry-standard pulse oximetry devices, and for the assessment of the Air Next spirometer, participants will host the mobile spirometer at home for once daily measurements. Measurements will be validated at Study Center visits using an industry-standard device before and after the use of a bronchodilator.

**Table 1 table1:** Schedule of study activities.

		Device assessment period			Clinical feasibility study period				
	Screening	Baseline visit	Interim visit	Final visit	Interim visits			Final visit	
Visit	1	2	3	4	5	6	7		8
Days	1	7	14	21	28	35	56		90
Informed consent process	✓								
Study eligibility and smoking status	✓								
Reviewing medical history (including physical examination and BMI^a^ measurement)	✓	✓	✓	✓	✓	✓	✓		✓
COPD^b^ assessment test	✓	✓	✓	✓	✓	✓	✓		✓
Spirometry	✓	✓	✓	✓	✓	✓	✓		✓
6-minute walk test	✓	✓	✓	✓	✓	✓	✓		✓
Providing the study requirements handout and explaining the study/visit requirements	✓	✓	✓	✓	✓	✓	✓		✓
Dichotomous questionnaire for visit readiness	✓								
Providing mHealth^c^ devices	✓								
Assessment of AnaMed OEM^d^ device		Continuous monitoring							
Assessment of Air Next mobile spirometer against standard		Continuous monitoring							

^a^BMI: body mass index.

^b^COPD: chronic obstructive pulmonary disease.

^c^mHealth: mobile health.

^d^OEM: original equipment manufacturer.

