### Data Management

All study data will be stored in the information technology Unit of the Kazakhstan Academy of Preventive Medicine. Verification of eligibility was completed via a web questionnaire after participants signed the consent form, and participants will be tracked for the completion of all the study data. If a participant is excluded or discontinues use during or after the study procedures, the specific exclusion or discontinuation reason will be recorded in the database.

All electronic files are encoded using a 128-bit advanced encryption standard and are password protected on a computer with both hardware and software firewalls. The locator form and any documents with identifying information are kept in a separate folder and kept locked in filing cabinets.

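### The primary recruitment rate is defined on people screened but planned on people invited; the two denominators differ and need to be reconciled

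*Protocol article*

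**What the plan says.** All places are in the Methods of the protocol article.

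- **Outcome Measures** makes recruitment one of the primary measures and defines it: "Recruitment is defined as the number of potential participants screened for study eligibility versus the number of people who enrolled in the study". Taken literally the ratio is in reverse order; I read it as enrolled divided by screened.
- **Sample Size Calculation** lists the same endpoint and gives its planning value: "We conservatively predict that 30% of the people invited to participate will be recruited to the study, with a 95% CI of 13-47" per cent. It also says "we plan to recruit 27 participants" and "All calculations are based on two-way 95% confidence intervals".
- **Data Management** gives the order of steps: "Verification of eligibility was completed via a web questionnaire after participants signed the consent form".
- **Table 1 (Study Procedures, Overview)** has the row "Informed consent process" ticked at the screening visit only, the same visit as the eligibility check.
- **Participant Recruitment and Registration** describes nonprobability sampling, "including quota and snowball sampling methods".

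**The concern.** One primary endpoint has two denominators. They agree only if everyone who is invited goes on to be screened. Because consent comes before the eligibility check, a person who turns down the invitation or does not sign would ordinarily not be counted as screened. The rate in Outcome Measures then shows how many willing people pass screening. The rate in the Sample Size Calculation shows how many of those approached end up in the study.

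The study is meant to show whether a large study is feasible and to inform its design. Anyone planning that study needs to know how many people must be approached per participant enrolled. If a screening yield is read as that figure, the number will be set too low. If it is placed beside the 30% prediction, recruitment may look better than expected only because the denominator changed.

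**Working it through.** **Inputs from the Sample Size Calculation:** 27 to be enrolled; predicted recruitment 30% of people invited; stated 95% interval 13-47%; two-sided 95% intervals throughout. The share of invitees who reach screening is not given and is assumed below.

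**Step 1: reproduce the stated interval.** Simple (Wald) interval, p ± 1.96 × √(p(1 − p)/n).
- p = 0.30, n = 27: half-width 1.96 × √(0.21/27) = 0.173, so 12.7% to 47.3%. This matches 13-47%.
- The same formula with n = 27 gives ±13.5 points for 85% retention (stated ±13%) and ±17.3 points for 70% adherence (stated 17%). This is the method the plan used.

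For retention and adherence, 27 enrolled is the right denominator. For recruitment it is not: 27 is the numerator of the rate. If 27 were the number invited, 30% would give only 0.30 × 27 = 8.1 enrolled, against the 27 planned.

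**Step 2: the interval on people invited.**
- Implied number invited: 27/0.30 = 90.
- Half-width 1.96 × √(0.21/90) = 0.095, so 20.5% to 39.5%. The exact binomial interval for 27/90 is 20.8% to 40.6%.

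**Step 3: the rate as Outcome Measures defines it.** Keep 27 enrolled and 90 invited, so the invited-based rate is 30%, and vary the number screened.

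| Screened (assumed) | Share of the 90 invited | Enrolled/screened | Multiple of 30% |
|---|---|---|---|
| 90 | 100% | 27/90 = 30% | 1.0 |
| 81 | 90% | 27/81 = 33% | 1.1 |
| 63 | 70% | 27/63 = 43% | 1.4 |
| 45 | 50% | 27/45 = 60% | 2.0 |
| 36 | 40% | 27/36 = 75% | 2.5 |

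The multiple is 90 divided by the number screened, so it cannot fall below 1 when those screened come from those invited. The rate passes the stated upper limit of 47% once 57 or fewer of the 90 (63%) are screened: 27/57 = 47.4%, against 27/58 = 46.6%.

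**The case against.** Enrolled/screened is a legitimate recruitment measure, and Outcome Measures states its denominator openly. It is not a biased estimator of itself; it is higher only in relation to a different quantity. That stands, and it is why the point concerns two definitions that do not match.

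A reader might infer more than the documents support:

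- **That refusals can never enter the denominator.** Signed consent and willingness to be trained are themselves inclusion criteria, so someone who attends the visit and declines could be recorded as screened and ineligible. Table 1 does not order the steps within the visit. Data Management makes consent-first the natural reading, but it does not exclude counted contact before consent.
- **That 30% is a target.** It is worded as a prediction and used for precision. No go/no-go rule is attached, and no section says the result will be judged against it.
- **That the rate will be inflated by a particular large factor.** Any factor depends on the assumed share reaching screening; at 90% it is only 1.1.
- **That quota sampling distorts the rate further**, because eligible volunteers for a full cohort would count as not recruited. The article names the method but does not say that screening continues for a filled cohort or how such people are counted.

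It is also fair to say that a journal article condenses the full protocol, so an invitation log may exist elsewhere; its absence here is not the finding. Finally, a rate from quota and snowball sampling at one centre may transfer poorly to a larger study with either denominator. None of this removes the conflict between the two sections.

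**Conclusion.** The concern holds as an inconsistency in a primary endpoint. Outcome Measures and the Sample Size Calculation describe different quantities under one name. On the natural reading of Data Management, the defined rate leaves out people who decline before screening. It is therefore a screening yield, equal to the invited-based rate if nobody drops out before screening and higher otherwise.

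The direction follows from the documents; the size does not. At the plan's own 27 enrolled and implied 90 invited, an assumed 40-90% of invitees reaching screening gives 75% down to 33% in place of 30%.

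The precision statement has a related fault that needs no such assumption. The 13-47% interval uses the number enrolled as its denominator. On the number invited it is about 20-40%, narrower than stated, so the sample size itself is not put in doubt.

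**What to change.** 1. In Outcome Measures, define recruitment as enrolled divided by invited.
2. Keep a log of everyone approached and of refusals, and ask participants to report the people they refer under snowball sampling.
3. Report the overall sequence of invited, consented, eligible and enrolled. Break it down by cohort only from the step at which cohort is known: asymptomatic and grey-zone status depend on spirometry, symptom score and walk test done at screening, so people who decline earlier cannot be assigned.
4. Report enrolled/screened separately as screening yield, and do not compare it with the 30% prediction.
5. Where earlier or snowball invitations cannot be counted, say so and label the rate as screening yield.
6. In the Sample Size Calculation, restate the recruitment interval on the number invited (about 20-40% for 27/90).

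**Cost:** one changed definition, one recomputed interval and a log kept by recruiting staff with participants' help. The reported rate will be lower than the screening yield. Some snowball invitations may be missed, and because inclusion began in June 2019, some earlier invitations may not be recoverable.
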